**Fig. 1 Fig1:**
[figure not shown]
Timeline and schematic overview of the HIPPROCLIPS-trial. Legend: Main statistical methods are in italic. THA = total hip arthroplasty

### Participants

Two-hundred participants will be recruited from a secondary care setting at Hospital East-Limburg in Genk (Belgium) and the European Hip Clinic in Herselt (Belgium) starting from May 2021. Persons with a confirmed clinical or radiographic primary diagnosis of hip OA who are on the waiting list for a THA will be invited to participate in this study. Exclusion criteria are (1) rheumatic arthritis or other rheumatic diseases, (2) avascular necrosis or other pathological conditions explaining the symptoms, (3) neurological disorders (e.g., Parkinson’s disease, dementia…) significantly influencing the symptoms of hip OA, (4) revision THA, (5) a history of pathological fractures (e.g., osteoporosis, tumour…), (6) other planned surgical procedures during the follow-up period of twelve months (e.g., contralateral THA, TKA…). All participants will have to provide written informed consent before being included in the study.

Quantitative Sensory Testing (QST)	Cold detection threshold (CDT) (local, remote)	T0, T2, T3, T4
	Warmth detection threshold (WDT) (local, remote)	T0, T2, T3, T4
	Cold Pain Threshold (CPT) (local, remote)	T0, T2, T3, T4
	Heat Pain Threshold (HPT) (local, remote)	T0, T2, T3, T4
	VAS 60 Temperature	T0, T2, T3, T4
	Temporal Summation of Pain (TSP)	T0, T2, T3, T4
	Conditioned Pain Modulation (CPM)	T0, T2, T3, T4
**Outcome variables**	**Variables**	**Timepoints**
Self-reported pain and disability	Hip disability and Osteoarthritis Outcome Score (HOOS) [62]	T0, T2, T3, T4
	Patient Specific Functioning Scale (PSFS) [63]	T0, T2, T3, T4
	Numerical Pain Rating Scale (NPRS) [64]	T0, T1, T2, T3, T4
Health-related quality of life	36-item Short-Form Health Survey (SF-36) [65]	T0, T2, T3, T4
Effect of THA on hip complaints in general	Global Perceived Effect (GPE) [66]	T0, T1, T2, T3, T4
Satisfaction with the outcome after THA	Satisfaction (NRS)	T0, T1, T2, T3, T4
Performance-based measures (PBM) [67]	30 s chair stand test (30s-CST)	T0, T2, T3, T4
	40 m fast paced walk test (40 m FPWT)	T0, T2, T3, T4
	10-step stair climb test (10-step SCT)	T0, T2, T3, T4
Muscle strength testing [68]	Isometric muscle strength of the hip flexors, extensors, abductors, adductors, external rotators	T0, T2, T3, T4

### Phenotyping variables/candidate prognostic factors

#### Sociodemographic and biomedical information

Participants will be asked to indicate their age, gender, height (m), body weight (kg), smoking status, educational level, marital status, and employment status. Self-reported height and body weight will be used to calculate Body Mass Index (BMI)(kg/m^2^). The number of comorbidities will be evaluated using a standardized self-created list of common comorbidities (heart disease, diabetes, psychiatric disorders, epilepsy, cancer, hypertension, major surgery in the past, osteoporosis, joint replacement, or other comorbidities). Additionally, participants will have to indicate whether they perform sports (activities that are intense enough so that one sweats at least to a slight degree from them) on a regular basis (yes/no), and whether they have previously received physiotherapy treatment for their hip complaints (yes/no). The number of physiotherapy sessions will be registered, as well as the type of physiotherapy exercises and treatments (e.g. education, strengthening exercises, cardiovascular exercise…). Finally, participants will be asked whether they received any psychological therapy during the follow-up period, and which type of psychological therapy they received.

#### Pain-related cognitions and emotions

Fear-avoidance will be assessed by the Dutch version of the Fear-Avoidance Components Scale (FACS-D) [51], which is a 20-item questionnaire. Each item is scored on a six-point Likert scale, resulting in scores ranging from zero (“completely disagree”) to five (“completely agree”). There is a maximum total score of 100, with higher scores indicating more fear-avoidance. Five severity levels have been proposed: subclinical (0–20), mild (21–40), moderate (41–60), severe (61–80), and extreme (81–100) [52]. The FACS-D has good reliability and validity in persons with chronic musculoskeletal pain, including persons with chronic hip pain [51].

Pain-related fear of movement and (re)injury will be assessed with the 17-item version of the Tampa Scale for Kinesiophobia (TSK-17) [53]. Each item is scored on a four-point Likert Scale, ranging from one (“strongly disagree”) to four (“strongly agree”). The total score ranges between 17 and 68, with higher values reflecting greater fear of movement. Measurement properties of the TSK-17 are sufficient in patients with chronic musculoskeletal pain [54–58].

Perceived injustice will be measured with the Injustice Experience Questionnaire (IEQ) [59]. The IEQ consists of 12 items, each item is scored from zero (“not at all”) to four (“all the time”). The total score ranges between zero and 48 and higher total scores reflect higher levels of perceived injustice. The validity of the IEQ is sufficient in patients with musculoskeletal pain [59].

#### Traumatic experiences

The Dutch version of the Childhood Trauma Questionnaire (CTQ) will be used to assess whether participants had a history of abuse or neglect in childhood [60, 61]. The CTQ consists of 25 items which evaluate childhood maltreatment across five dimensions: (1) physical abuse; (2) physical neglect; (3) emotional abuse; (4) emotional neglect; and (5) sexual abuse. Each item is scored on a five-point Likert scale, ranging from one (“never true”), to five (“very often true”). The total score ranges from 25 to 125, and each subscale score ranges from five to 25. The Dutch version of the CTQ was found to be valid and reliable [61].

The Traumatic Experiences Checklist (TEC) is a self-reported questionnaire to evaluate a persons’ history of traumatic experiences. The Dutch TEC will be used to evaluate a wide range of potential traumatizing experiences (29 types) [62]. The checklist covers traumatic experiences in six areas: (1) emotional abuse; (2) emotional neglect; (3) sexual harassment; (4) sexual abuse; (5) physical abuse; and (6) threat to life or bizarre punishment/intense pain. Furthermore, 11 items relating to family events are included, such as a divorce or loss of a significant other. Participants have to indicate whether or not they experienced a traumatic event, the age at onset, the duration of the trauma, and the subjective impact of the traumatic event, ranging from one (“no impact”) to five (“very severe impact”). The total score ranges from zero to 29 and indicates the number of traumatic experiences. Psychometric properties of the TEC were found to be good [63].

#### Mental disorders

The Mini International Neuropsychiatric Interview Simplified (MINI-S) for the Diagnostic and Statistical Manual of Mental Disorders 5 (DSM-5) will be used to identify psychiatric comorbidity [64]. The MINI-S is a brief semi-structured diagnostic interview for the major psychiatric disorders in the DSM-5. The MINI-S assesses the 17 most common disorders in mental health. Additionally, the suicidal risk module of the MINI-S DSM-4 will be administered [65, 66].

The Hospital Anxiety and Depression Scale (HADS) will be used to screen for symptoms of anxiety and depression. The HADS is a 14-item questionnaire evaluating symptoms of anxiety and depression without involving physical complaints [67]. One subscale covers symptoms of anxiety (HADS-A), the other symptoms of depression (HADS-D). Each item is scored from zero (”not applicable”) to three (”certainly applicable”). The maximum score on each subscale is 21, with higher values indicating more anxiety/depression symptoms. Both the anxiety and depression subscales have good psychometric properties in musculoskeletal pain populations [68].

#### Self-efficacy

The General Self-Efficacy Scale (GSES) is a self-reported questionnaire used to measure self-efficacy [69]. The GSES measures how a person generally copes with stressors/difficult situations in life. It consists of ten statements (optimistic “self-beliefs”) that ask about how people think and act in general. Items are scored on a four-point Likert scale.

#### Perceived stress

Perceived stress will be evaluated with a single question from the Perceived Stress Scale (PSS): “In the last month, how often have you felt nervous and stressed?” [70]. The question is scored on a five-point Likert scale, ranging from zero ‘never’ to four ‘very often’. The PSS has been found to be reliable and valid in different populations [71].

#### Social support

The Groningen Orthopaedic Social Support Scale (GO-SSS) is a self-reported questionnaire that has been developed to measure social support in patients with a THA or TKA [72]. Social support is measured through 12 statements, and each item is scored on a four-point Likert scale ranging from one (“never or rarely”) to four (“often”), resulting in a total score ranging from zero to 48. Validity and reliability of the GO-SSS were found to be sufficient for individuals undergoing total hip or knee arthroplasty [72].

#### Other pain-related variables

Participants will be asked to indicate their pain duration (months), use of pain medication (none, seldom, most days and/or nights, all days and/or nights), number of painful body regions (last week and last year) assessed with a self-created list of body regions, and the number of painful days last week.

#### Quantitative sensory testing (QST)

Quantitative sensory testing (QST) can be used to measure peripheral and central somatosensory function in persons with musculoskeletal pain [73, 74]. A Peltier-based computerized thermal stimulator (TSA II; Medoc Ltd, Ramat-Ishay, Israel) will be used to perform QST measurements. The TSA II uses thermal stimulation to assess the functionality of small nerve fibers and gain insight into the physiological and psychological processes underlying pain and sensation responses. The standardised QST protocol that is described below, including measures of local and widespread hypo- and hyperalgesia, temporal summation of pain, and conditioned pain modulation, will be performed in all participants. Heat and cold stimuli will be applied by means of a 30 × 30 mm thermode. The baseline temperature will be set to 32 °C for all these measurements.

The protocol of the German Research Network on Neuropathic Pain (DFNS) will be followed to determine thermal detection and pain thresholds [75]. Cold detection thresholds and warmth detection thresholds (in °C) will be assessed locally (at the most painful site of the hip) and remotely (at the volar aspect of the contralateral wrist) using a limits protocol (rate of 1 °C/s, interstimulus interval 4s). Cold pain thresholds and heat pain thresholds (in °C) will be assessed locally (at the most painful site of the hip) and remotely (at the contralateral wrist) using a limits protocol (rate of 1 °C/s, interstimulus interval 10s). Four trials will be performed for each threshold. The first trial will be used to give the patient a sense of what is expected. The average temperature of the last three trials will be calculated to define the specific threshold.

To determine the temperature that corresponds with a visual analogue scale (VAS) score of 60, a VAS Search protocol will be performed at the volar aspect of the contralateral wrist. The thermode will repeatedly heat up from the baseline temperature (32 °C) to a temperature between 39 and 50 °C. Participants will have to indicate their pain intensity for these stimulus intensities on a scale from zero, “no pain”, to 100, “worst imaginable pain”. Depending on their pain intensity, the thermode will heat up to a higher or lower temperature until the participant indicates a VAS of 60 out of 100. The temperature corresponding to a VAS 60 is determined to be used in the dynamic QST-protocols for the evaluation of temporal summation and conditioned pain modulation, with a maximum of 45 °C.

Temporal summation of pain will be assessed at the contralateral wrist using a two-minute tonic heat stimulus and participant-controlled temperature [76]. Participants are presented with a tonic heat stimulus and are instructed to maintain their initial sensation for two minutes by increasing or decreasing the temperature (rate of 1 °C/s) via the response unit. To quantify temporal adaptation and temporal summation of pain, the magnitude of temperature changes will be extracted and the areas under the curve will be calculated.

Conditioned pain modulation will be evaluated using a Dual-Thermode program with two heat stimuli [77]. The test stimulus will be a heat stimulus administered twice at the volar aspect of the contralateral wrist. Once on its own before administering the conditioning stimulus (interstimulus interval 10s), and once at the end of the conditioning heat stimulus at the volar aspect of the ipsilateral wrist. The conditioning stimulus will be a heat stimulus administered at the volar aspect of the ipsilateral wrist after first applying the test stimulus. The difference in pain intensity at the contralateral wrist during the stand-alone test stimulus and the test stimulus during the conditioning stimulus will be calculated. Pain intensity is assessed using a VAS ranging from zero to 100, where zero stands for “no pain”, and 100 for “worst imaginable pain”.

### Outcome variables

#### Disability

Perceived disability will be assessed with the Hip disability and Osteoarthritis Outcome Score (HOOS), a self-reported questionnaire for evaluating symptoms and disability in persons with hip complaints [78, 79]. The HOOS has been validated in Dutch [80] and consists of 40 items, divided into five subscales: symptoms (five items), pain (ten items), functioning in activities of daily living (17 items), functioning in sport and recreation (four items), and quality of life (four items). Each question is scored on a five-point Likert scale, in which a higher score reflects fewer complaints. The total score of the HOOS ranges from zero to 100, and a higher score indicates lower disability. A normalized score from zero to 100 is calculated for each subscale as well. The Dutch version of the HOOS was found to be valid and reliable in individuals with OA [81].

The Patient Specific Functioning Scale (PSFS) will be used to evaluate the functional status of the participants within the ICF activity and participation domain [82]. The participants will be asked to name the three most important activities that are difficult or impossible to perform due to the hip problems. The participant will have to score the degree of impairment in the activities on an 11-point NRS scale, ranging from zero “cannot perform the activity” to ten “can perform the activity just as well as before occurrence of the hip problem”.

The Osteoarthritis Research Society International recommended minimum core set of performance-based outcome measures (PBMs), including the 30 s chair stand test, the 40 m fast paced walk test, and the 10-step stair climb test, will be performed to evaluate physical function [83]. Movement quality during the performance-based tests will be assessed based on acceleration data measured with an Inertial Measurement Unit [84]. The 30-second Chair Stand Test will be used to assess sit-to-stand activity. The maximum number of chair stand repetitions within 30 s will be used as the outcome value. The 10-step Stair Climb Test will be used to assess ascending and descending stair activity. The time in seconds to ascend and descend ten stairs will be used as the outcome value. The 40-meter (4 × 10-meter) Fast Paced Walk Test will be used to assess short distance walking activity. The time in seconds to walk four times ten meters for a total of 40 m will be used as the outcome value.

#### Pain

The average pain intensity over last week and the current pain intensity will be assessed by the Numeric Pain Rating Scale (NPRS), an 11-point scale ranging from zero (“no pain”) to ten (“worst possible pain”)[85]. The NPRS has appropriate measurement properties in patients with musculoskeletal pain [86, 87].

#### Quality of life

The 36-item Short Form Health Survey will be used to evaluate health-related quality of life. The questionnaire is divided in eight health-related dimensions: physical functioning, role limitations due to physical problems, role limitations due to emotional problems, pain, mental health, energy, general health perception, and social functioning. A higher score indicates better health-related quality of life. The Dutch version of the SF-36 was found to be a valid and reliable instrument in individuals with different chronic diseases [88].

#### Muscle strength

Hip muscle strength will be measured with the MicroFet 2®, a handheld dynamometer. In the test protocol, the following muscle groups will be tested consecutively: abductors (side lying), adductors (supine), extensors (prone), hip flexors (sitting), external rotators (sitting). Each muscle group will be tested three times, with the best value of the three tests as the final result [89].

#### Other outcome variables

Satisfaction will be assessed with an 11-point Numeric Rating Scale (NRS), ranging from zero (“not satisfied”) to ten (“very satisfied”). The participant’s opinion about recovery after THA will be evaluated using the Global Perceived Effect score on a seven-point Likert scale, ranging from zero “a lot worse” to seven “a lot better” [90].

### Statistical analysis

Statistics will be performed in R (Version 3.6.3) using RStudio (2022.07.2). According to the different research questions and the type of data available, different statistical methods will be used (see Table 1). A sample size calculation was performed in R based on the third objective to identify pre- and early postoperative prognostic factors for long-term outcomes in pain and disability after THA for hip OA. A sample size of 200 participants will be needed for a prognostic model with 12 independent variables, a power of 80%, an effect size of 0.15, and a drop out of 20%.

For study 1, a LASSO regression (Least Absolute Shrinkage and Selection Operation) analysis will be used to assess the potential relationship between traumatic experiences and mental disorders on pain processing variables (QST) [91]. LASSO regression is a technique that extends the traditional linear regression by incorporating a regularization term that penalizes the size of the regression coefficients. This penalty aids in reducing model complexity and identifying the most essential predictors. When working with high-dimensional data containing numerous predictor variables, LASSO regression is particularly useful. LASSO is superior to traditional linear regression in its ability to prevent overfitting, enhance model interpretability, and reduce estimate variance.

If no suitable model (autocorrelation, residual distribution) can be found, a neural network will be used to answer this research question [92].

In study 2, since all pre-operative phenotyping variables will be included in the model, decision tree learning will be used to select the most relevant variables to include in the model to identify preoperative clinical phenotypes [93]. Decision tree learning is a type of machine learning algorithm that constructs a tree-like model of decisions. An important distinction between decision tree learning and traditional linear regression is that decision trees can deal with both categorical and continuous data, whereas linear regression requires that independent variables be continuous. In addition, decision trees can account for non-linear correlations between variables and interactions among predictors. Moreover, decision trees are easier to interpret than linear regression models. The structure of the decision tree is readily comprehensible, as are the rules for predicting outcomes.

If this approach is not successful, random decision forest will be used [94]. However, it is preferred to keep the model as simple as possible to ease the clinical interpretation.

For the study 3 gradient boosting algorithms will be applied to the dataset to select the best prognostic factors for long-term outcomes in terms of pain and disability [95]. Gradient boosting techniques are a type of ensemble learning that combines numerous weak predictors to create a more accurate one. It adds decision trees to the model in an iterative manner, with each new tree aiming to correct the errors of the preceding trees. Gradient boosting algorithms are especially effective when working with complex data and are frequently capable of achieving high accuracy on a wide variety of problems compared to stepwise linear regression. Previous contralateral THA will be included as a covariate in the analysis to account for possible bias due to knowledge of surgical procedures and postoperative recovery course.

Finally, for study 4, recurrent neural networks (RNN) will be applied to identify postoperative clinical phenotypes based on the multiple data points (repeated measurements during T2, T3, and T4) [96]. RNNs are a sort of neural network architecture that can process sequences of inputs, such as time series. They can keep an internal memory of previous inputs and use it to make predictions about future inputs. RNNs are particularly good for modelling complex temporal interactions. When working with sequential data, RNNs tend to be more flexible and robust than stepwise regression. They are able of modelling complex temporal relationships and less susceptible to overfitting.

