2	To identify preoperative clinical phenotypes in individuals with hip OA and their prognosis for outcomes in pain and disability after THA	1. Which clinical phenotypes exist in individuals with hip OA waiting for THA, based on a set of biopsychosocial characteristics? 2. What is the prognostic value of these clinical phenotypes for outcomes in pain and disability after THA?	- Sociodemographic and biomedical information (T0) - Pain-related cognitions and emotions (T0) - Traumatic experiences (T0) - Mental disorders (T0) - Self-efficacy (T0) - Social support (T0) - Perceived stress (T0) - QST (T0) - Other pain-related variables (T0)	Primary: HOOS Secondary: NPRS, PBM, SF-36, PSFS, GPE, Satisfaction, Muscle Strength	**Design**: Cross-sectional analysis of baseline data **Main statistical method**: Decision Tree learning
3	To identify pre- and early postoperative prognostic factors for long-term outcomes in pain and disability after THA in individuals with hip OA	1. To which extent do pre-operative traumatic experiences, mental disorders, pain-related cognitions and emotions, self-efficacy, social support, and central pain mechanisms predict long-term postoperative pain and disability after THA for hip OA? 2. To which extent do early postoperative pain-related cognitions and emotions predict long-term pain and disability after THA for hip OA?	- Pain-related cognitions and emotions (T0) - Traumatic experiences (T0) - Mental disorders (T0) - Self-efficacy (T0) - Social support (T0) - QST (T0)	Primary: HOOS Secondary: NPRS, PBM, SF-36, PSFS, GPE, Satisfaction, Muscle Strength	**Design**: longitudinal prospective **Main statistical method**: Gradient Boosting Algorithms

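### The 80% power given for 200 participants refers to a 12-variable model, not to the gradient-boosting selection planned for Study 3, and the stated inputs do not lead to 200

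*Protocol article*

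**What the plan says.** The Statistical analysis section of the protocol article ties the sample size to Study 3: "A sample size calculation was performed in R based on the third objective to identify pre- and early postoperative prognostic factors". The result is "A sample size of 200 participants will be needed for a prognostic model with 12 independent variables", with "a power of 80%, an effect size of 0.15, and a drop out of 20" per cent. It does not name the type of model, the test, alpha, the effect-size metric or the 12 variables.

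For the analysis of Study 3, the same section says that "gradient boosting algorithms will be applied to the dataset to select the best prognostic factors for long-term outcomes in terms of pain and disability". It adds previous contralateral THA as a covariate.

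Table 1 (Study design) gives the Study 3 candidates as "Pain-related cognitions and emotions (T0) - Traumatic experiences (T0) - Mental disorders (T0) - Self-efficacy (T0) - Social support (T0) - QST (T0"). The second research question of Study 3 in that table also asks about early postoperative pain-related cognitions and emotions. The Study design section has questionnaires completed on four days of the first postoperative week. Table 2 (Procedure) lists the individual variables within each domain.

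**The concern.** A power figure describes one test in one model. Here a figure for a 12-variable model supports an analysis of a different kind, applied to a candidate set that the article never reduces to 12. Boosting-based selection involves no hypothesis test with a rejection probability of 80%. Even for a regression, power for the whole set of predictors says little about finding any one of them, and finding individual factors is the stated objective.

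Study 3 is the only objective with a sample-size basis. The Discussion expects its factors to help identify persons at risk of poor outcome and to inform shared decisions. A reader could take the 80% as the chance of detecting a given prognostic factor, which it is not.

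**Working it through.** **Inputs.** From the Statistical analysis section: 12 independent variables, 80% power, effect size 0.15, 20% dropout, 200 participants. This leaves 200 × 0.8 = 160 analysed. My assumptions, because the article is silent: the effect size is Cohen's f², alpha is 0.05, and the test is the overall F test of a linear regression.

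**Formula.** With u predictors and n analysed, power = P(F′ > F_crit), where F′ is noncentral F with u and n − u − 1 degrees of freedom and noncentrality λ = f² × n. Enrolment = n / (1 − 0.2).

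**1. The plan's own figure.** For u = 12, n = 126 gives 79.8% and n = 127 gives 80.2% (λ = 0.15 × 127 = 19.05). So 127 must be analysed, and 127 / 0.8 = 158.75, or 159 enrolled. The stated 200 is not reproduced. Other readings:

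- Multiplying by 1.2 for dropout: 153.
- 0.15 as R²: 138. As f: 978. As r: 955.
- Alpha 0.025: 184. Alpha 0.01: 214, or 206 with the 1.2 multiplier.
- 90% power instead of 80%: 157 analysed, 197 enrolled.
- 21 predictors instead of 12: 160 analysed, exactly 200 enrolled.

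The last two come close or match, but each replaces a stated input. The article does not show which, if either, lies behind the 200.

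**2. Candidates from Tables 1 and 2, one score per instrument.**

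- Pain-related cognitions and emotions: FACS-D, TSK-17, IEQ = 3
- Traumatic experiences: CTQ, TEC = 2
- Mental disorders: MINI-S, suicidal risk, HADS = 3 (4 with HADS-A and HADS-D separate)
- Self-efficacy and social support: GSES, GO-SSS = 2
- QST: four thresholds at two sites = 8, plus VAS 60, TSP and CPM = 11

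Total: 3 + 2 + 3 + 2 + 11 = 21, or 22 with two HADS scores. The contralateral-THA covariate makes 22 or 23. Early postoperative FACS-D, TSK-17 and IEQ add 3 × 4 = 12 if each day is a separate term (34 or 35), or 3 if averaged over days (25 or 26).

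**3. Overall power at 160 analysed (λ = 0.15 × 160 = 24).**

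| Predictors | Power | Analysed for 80% | Enrolled |
|---|---|---|---|
| 12 | 90.9% | 127 | 159 |
| 21 | 80.2% | 160 | 200 |
| 22 | 79.0% | 163 | 204 |
| 23 | 77.8% | 166 | 208 |
| 26 | 74.3% | 175 | 219 |
| 35 | 64.4% | 201 | 252 |

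**4. Power for one factor.** If 12 uncorrelated predictors share f² = 0.15 equally, each has 0.15 / 12 = 0.0125 and λ = 0.0125 × 160 = 2.0. On 1 and 147 degrees of freedom, power is 29% at alpha 0.05 and 7% at 0.05 / 12.

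None of these is the power of boosting-based selection, for which no closed formula applies.

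**The case against.** Four points can be made for the plan.

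*A 12-variable reading exists.* The first Study 3 question speaks of central pain mechanisms, not of all QST. If that means TSP and CPM, and HADS counts as one score, there are 3 + 2 + 3 + 2 = 10 questionnaire and interview scores plus 2, which is 12. This stands as a possibility. It uses up all 12 before the contralateral-THA covariate and every early postoperative factor, although the calculation is tied to an objective that includes them. It also narrows Table 1, which lists QST without restriction, and the Background counts widespread hyperalgesia among the central indicators.

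*The larger counts are a tally.* This also stands. Neither 22 nor 35 appears in the article, and 22 is not a floor. The 35 requires both research questions in one model and each postoperative day as its own term, and the article says neither. A reader might infer that the study is clearly too small. The documents do not support that: counting every baseline candidate leaves linear-model power at about 78–80%, and 64% is a worst case.

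*The details may lie elsewhere.* An article may leave the list of 12, the tuning and the resampling to a fuller document. I therefore make no point of missing error control or unstable selection. The article also acknowledges that it has no external validation and that replication is needed. But the power figure and the planned method both stand in this text and do not match.

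*Boosting is a legitimate choice.* A reader might conclude that it should give way to regression as the main analysis. Correcting a power statement does not require that.

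**Conclusion.** The concern holds in a limited form. The 80% attached to 200 participants describes neither the boosting analysis planned for Study 3 nor the chance of identifying any single factor. That conclusion needs no predictor count.

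The numerical part depends on f² = 0.15, alpha 0.05 and an overall linear F test, all inferred. On that basis, the stated inputs call for 159 enrolled, and 160 analysed would give 91% rather than 80% for 12 predictors. Allowing for all baseline candidates brings power back to about the stated level. Only adding early postoperative terms lowers it noticeably, to 74% with 26 terms and 64% with 35. The 29% for one factor also assumes equal, uncorrelated shares.

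The problem is thus what the figure can be claimed to mean, together with a sum that does not reproduce. It is not a demonstrated shortage of participants.

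**What to change.** Restate the sample-size paragraph so that it:

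1. names the model, test, alpha and effect-size metric, and corrects whichever stated input does not lead to 200;
2. lists the predictors counted, including previous contralateral THA and the early postoperative terms, and says whether the latter enter by day or as a summary;
3. gives the power that 160 analysed provides for that set;
4. says that this is a linear-model approximation for the overall test, not power for selecting single factors by boosting.

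Optionally, report the pre-named linear model with 95% confidence intervals alongside boosting, which need not become secondary.

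The cost is a revised paragraph, possibly a less favourable power statement, and one additional regression if the option is taken. No new data or participants are needed.
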